### Statistical analysis

The baseline characteristics of the participants in the two arms will be described using means with SD and proportions for continuous and categorical variables, respectively. The effect of the HealthCap telemedicine system on SBP measured by ABPM (our primary outcome) will be examined using analysis of covariance (ANCOVA) with baseline SBP measured by ABPM and the treatment group as the covariate, following the intention-to-treat (ITT) principle, that is, patients will be encouraged to conduct ABPM at 12 months regardless of whether they comply with the assigned intervention. A per-protocol (PP) analysis will be conducted for sensitivity analysis. PP analysis provides some protection for theoretical increases in the risk of type I errors (erroneously concluding non-inferiority). Our modified ITT (mITT) data comprised all patients according to and were included in the random allocation of complete data. We defined the PP population as participants who met the mITT definition but did not receive intervention treatments. Based on a previous meta-analysis, we set the non-inferiority margin for ABPM SBP at 2 mmHg [26]. We accepted the non-inferiority of telemedicine over usual care (in a 0.0125-level test after Bonferroni correction for multiple testing) if the lower bound of the two-sided 95% confidence interval (CI) (equivalent to the upper bound of the one-sided 97.5% CI) was within the non-inferiority margin. Subgroup analysis will be conducted in cases of unbalanced baseline characteristics and for patients with and without indications of a lower BP target (i.e. <130/80 mmHg). Additionally, missing data will be addressed through multiple imputation.

Qualitative data will be analysed by at least 2 investigators using inductive thematic analysis as described by Braun and Clarke [28]. Therefore, digital recordings will be transcribed verbatim. The recordings will be listened to several times, and the transcripts will be read and re-read by at least 2 investigators. After familiarisation, codes and then themes will be generalised. The investigator team will discuss the themes to determine and decide on any over-arching themes. The Consolidated criteria for Reporting Qualitative Research (COREQ) Checklist will be followed throughout the qualitative research part to ensure comprehensiveness and transparency in reporting qualitative findings [29].

Cost-effectiveness analysis will be performed from a societal perspective. We will collect direct medical costs (e.g. clinical visits) and direct non-medical costs (e.g. average HealthCap maintenance cost per person). Furthermore, self-reported indirect costs of productivity (mainly for absenteeism, using a human capital approach) and transportation to doctors’ visits will be recorded. Other cost items are listed in the section “Health service utilisations and cost”. Considering the targeted population (well-controlled hypertensive patients) and the nature of this study, we do not expect any changes in quality-adjusted life years (QALY). However, to confirm there is no intangible cost difference, we will use the 5-level EQ-5D (EQ-5D-5L) for QALY estimation. We will use a bootstrapping approach to assess the uncertainty of the incremental cost-effectiveness gain and to generate the cost-effectiveness acceptability curves to assess the estimated probability of cost-effectiveness in relation to possible values of the cost-effectiveness threshold.

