### Randomisation/blinding

Stratified randomisation with blocks of four or six will be used according to (i) the presence or absence of diseases that increased cardiovascular risk and required a lower BP target (<130/80 mmHg) (including DM, history of cardiovascular diseases, history of chronic kidney disease) and (ii) the number of anti-HT medications (<3 or ≥3) because the number of medications affects medication adherence and the likelihood of maintaining optimal BP control [17]. The randomisation sequence will be generated by an independent statistician, using the statistic programme Random Allocation Software, version 1.1.0, printed out, and sealed in light-opaque envelopes, which will only be opened by the research assistant after a participant’s eligibility is confirmed and the consent form is signed. Due to the nature of the intervention, blinding the investigators, participants, and healthcare providers will be infeasible after randomisation. However, the independent statisticians who will conduct the analysis will remain blinded.

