### Sample size calculation

According to existing literature, a minimal clinically meaningful difference was set at an SBP difference of 2 mmHg [26]. By further setting type I error at 5% and type II error at 20%, and a standard deviation (SD) of 10 mmHg on ABPM (this is our primary outcome, and we observed this SD in our previous local studies) [27], the required sample size for this non-inferiority RCT will be 309. At the maximum dropout rate of 15%, 364 patients are required.

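### The primary ANCOVA omits both randomisation strata; adding them is a free but minor improvement in precision

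*Protocol article*

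**What the plan says.** The Randomisation/blinding section of the protocol article defines the design. It opens with the comorbidity factor: "Stratified randomisation with blocks of four or six will be used according to (i) the presence or absence of diseases that increased cardiovascular risk". Next comes drug number, stated together with its rationale: "the number of anti-HT medications (<3 or ≥3) because the number of medications affects medication adherence and the likelihood of maintaining optimal BP control". A reason tied to outcome is given for the second factor. The first is described by the lower target that these patients require.

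The Statistical analysis section names the primary model: "analysis of covariance (ANCOVA) with baseline SBP measured by ABPM and the treatment group as the covariate". The lower-target factor returns in that section only to define a subgroup analysis. The drug-number factor does not return. No other section adds either factor to the primary model.

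The same section fixes the criterion against which precision matters: "we set the non-inferiority margin for ABPM SBP at 2 mmHg".

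**The concern.** Permuted blocks within strata hold the stratification factors nearly equal between arms, so the treatment estimate varies less from trial to trial than under simple randomisation. A model without the strata does not know this. It leaves whatever the strata explain in the residual variance, and its standard error then overstates the real sampling variability. The interval is too wide and the actual error rate falls below its nominal level.

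In a non-inferiority trial with a 2 mmHg margin, the cost is a somewhat lower chance of showing non-inferiority when it is true. The article names its covariates rather than leaving them open, so an analysis plan that follows it would repeat the omission.

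**Working it through.** **The article's own figure.** Sample size calculation gives margin 2 mmHg, SD 10 mmHg, type I error 5%, power 80%, and a requirement of 309, or 364 after 15% dropout. With one-sided 5%, n = 2 × 10² × (1.645 + 0.842)² / 2² = 309.1, and 309 / 0.85 = 363.5, rounded up to 364. The formula yields a number per arm, whereas the article uses 364 as the trial total. That is a separate and much larger matter. Here I take 309 evaluable in total, because that is how the trial will run.

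**Inputs from the article.** N = 309, SD = 10, margin = 2, 1:1 allocation. I use one-sided 0.025, which matches the two-sided 95% interval in the decision rule. The same sentence also mentions a 0.0125-level test, so I vary this below.

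**Assumptions not in the article.** These are the correlation ρ between baseline and 12-month daytime SBP (0.5 here) and R², the share of variance left after baseline SBP that the two strata explain (0% to 10%). The true difference is set to zero for power.

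**Formulas.**
- Model SE without strata = 10 × √(1 − ρ²) × √(4/N) = 10 × 0.866 × 0.1138 = 0.985 mmHg
- True SE under stratified randomisation = 0.985 × √(1 − R²)
- SE excess = 1/√(1 − R²) − 1
- Power, strata omitted = Φ((2 − 1.96 × 0.985) / true SE)
- Power, strata included = Φ(2 / true SE − 1.96)
- Actual one-sided error, strata omitted = Φ(−1.96 / √(1 − R²))

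| R² | True SE | SE excess | Power omitted | Power included | Actual error |
|---|---|---|---|---|---|
| 0% | 0.985 | 0% | 52.8% | 52.8% | 2.5% |
| 2% | 0.975 | 1.0% | 52.8% | 53.6% | 2.4% |
| 5% | 0.960 | 2.6% | 52.9% | 54.9% | 2.2% |
| 10% | 0.935 | 5.4% | 52.9% | 57.1% | 1.9% |

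On the scale of the margin, including the strata moves the upper confidence limit by 1.96 × (0.985 − true SE). That is 0.02, 0.05 and 0.10 mmHg for R² of 2%, 5% and 10%.

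**Wider range.** With ρ from 0 to 0.7, one-sided alpha from 0.0125 to 0.05 and R² from 1% to 10%, the power lost by omission runs from about 0.2 to about 5 percentage points.

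**Simulation check.** There were 3,000 trials per setting, with 364 randomised in stratified blocks of four or six, 15% random dropout, ρ = 0.5 and one-sided 0.025.
- Assumed stratum effects of −4 and +3 mmHg beyond baseline. Without strata, the mean model SE was 1.02 against an empirical SE of 0.99, and power was 50.6%. With strata, the model SE was 0.99 and power 53.2%.
- No stratum effects. Model SE was 0.986 without and 0.987 with strata, and power was 50.5% and 50.3%. The simulation error on a power figure is about √(0.25/3000) = 0.9 points, so the two do not differ.

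The simulation agrees with the formulas in direction and rough size.

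**The case against.** The strongest objection is that the loss may be close to nothing. What counts is prediction beyond baseline SBP, which is already in the model, and the documents give no figure for it. Eligibility criteria sets a lower systolic entry limit for patients with comorbidities (130 rather than 135 mmHg), so the first stratum is tied to baseline SBP, which probably absorbs part of its effect. This stands, and it is why the range must start at zero.

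A reader might infer that the article declares both factors prognostic. It does so only for drug number, saying that "the number of medications affects medication adherence and the likelihood of maintaining optimal BP control". That speaks to adherence and keeping control, not to mean SBP given baseline. For comorbidity, prognostic value is an inference.

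A reader might also compute power from the unadjusted SE, 10 × √(4/309) = 1.138 mmHg, and report 42% rising to 43–46% for R² of 2–10%. Those figures assume no baseline correlation and so do not describe the stated ANCOVA, which adjusts for baseline.

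Finally, the article is condensed, its wording is loose (treatment group is called a covariate), and an analysis plan not shown could add the strata. This does not remove the point, because the covariates are named and the list departs from the design. It does keep the point minor.

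**Conclusion.** The mismatch between the stratified design and the stated primary model is real. Its effect is conditional and small. If the strata carry no information beyond baseline SBP, nothing is lost. If they explain 2% to 10% of the residual variance, the standard error is 1.0% to 5.4% too large and about 1 to 4 points of power are lost at ρ = 0.5 and one-sided 0.025. Because baseline SBP probably captures part of the lower-target factor, a loss of about 0 to 3 points is the more plausible range. All of this rests on assumed values of ρ and R².

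A reader might infer that the primary analysis is invalid, or that a non-inferiority claim would be unsafe. The documents support neither. The omission causes no bias, and any error is conservative, making a false claim of non-inferiority less likely. The low power in these illustrations comes from the sample size and should not be charged to this point.

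**What to change.** State the primary model as 12-month daytime SBP on treatment group, baseline daytime SBP, lower-target stratum (yes/no) and number of antihypertensive drugs (<3 or ≥3), with both strata entered as fixed covariates at the values used for randomisation. Use the same model in the per-protocol and multiple-imputation analyses.

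The cost is two degrees of freedom and a sentence of text, since both factors are recorded at randomisation. Make the change before any outcome comparison, so that the added covariates cannot look chosen after seeing results. Trial status reports 114 of 365 recruited, so there is time.

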### Criteria for discontinuing or modifying allocation

Participants are encouraged to adhere to their assigned allocation as closely as possible. If any of the answers to the safety questionnaire are positive or the mean BP value from 7-day HBPM is suboptimal, the patient in the intervention group will receive usual doctor consultation. This consultation is part of the intervention and does not constitute a modification of allocation. Although there are no criteria for allocation modification, participants may withdraw from the study at any time if they choose to.

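### The per-protocol set is defined as those who did not receive the intervention, which defeats its stated purpose of guarding against false non-inferiority

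*Protocol article*

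**What the plan says.** All of the relevant text but one sentence is in the Statistical analysis section of the protocol article.

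- Primary analysis: ANCOVA of 12-month daytime ambulatory systolic BP, adjusted for baseline, on the intention-to-treat (ITT) principle.
- Role of the PP analysis: "A per-protocol (PP) analysis will be conducted for sensitivity analysis".
- Reason given for it: "PP analysis provides some protection for theoretical increases in the risk of type I errors (erroneously concluding non-inferiority".
- Modified ITT (mITT) set, on which PP builds: "Our modified ITT (mITT) data comprised all patients according to and were included in the random allocation of complete data". The wording is garbled. The likely meaning is all randomised patients with complete data, analysed as allocated.
- PP set: "We defined the PP population as participants who met the mITT definition but did not receive intervention treatments". The article defines it nowhere else.
- Margin: "we set the non-inferiority margin for ABPM SBP at 2 mmHg".

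The section on criteria for discontinuing or modifying allocation also bears on who has received the intervention. When a HealthCap patient has a suboptimal home BP mean or a positive safety answer and is therefore seen by a doctor, "This consultation is part of the intervention and does not constitute a modification of allocation".

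**The concern.** A PP set keeps participants who received the strategy to which they were allocated. The article's definition keeps those who did not. In the HealthCap arm only non-users remain. Every control qualifies, because no control receives the intervention. Patients sent to a consultation by the algorithm count as having received the intervention, so they are dropped with the other users.

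This matters more in a non-inferiority trial than in a superiority trial. Non-adherence dilutes an ITT difference towards zero, which is the direction of a non-inferiority claim. The PP analysis is the check the article names against that. As defined, it contains nobody exposed to the strategy under test, so it carries the dilution to its extreme. A harmful effect of HealthCap among its users could not appear in it.

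**Working it through.** The article gives no figure for the PP set, so there is none to reproduce. The check compares the chance of wrongly showing non-inferiority under three analysis sets.

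**Inputs from the article**
- SD 10 mmHg (Sample size calculation).
- Margin 2 mmHg (Statistical analysis).
- 364 randomised 1:1 with 15% dropout: 364 × 0.85 ≈ 309 evaluable, about 154 per arm.
- One-sided 0.025, matching the two-sided 95% interval in the decision rule. The same section also names a test level ("in a 0.0125-level test after Bonferroni correction for multiple testing"), so 0.0125 is shown too.

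**Assumptions not in the article**
- A share p of the HealthCap arm does not take up the intervention. No rate is given, so 5% to 50% is shown.
- Non-users have the usual-care mean; users are worse by exactly 2 mmHg, the edge of the margin. Any claim of non-inferiority is then false.
- Apart from this, users and non-users do not differ from controls.
- The precision gain from baseline adjustment is ignored.

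**Formulas**

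SE = 10 × √(1/n₁ + 1/154), where n₁ is the number of HealthCap patients in the set.

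P(show non-inferiority) = Φ((2 − μ)/SE − z), with z = 1.96 at 0.025 and 2.24 at 0.0125.

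- PP as written: n₁ = 154p, μ = 0.
- PP corrected: n₁ = 154(1 − p), μ = 2.
- ITT: n₁ = 154, μ = 2(1 − p).

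**Worked case, p = 10%, one-sided 0.025**
- As written: n₁ = 15, SE = 10 × √(1/15 + 1/154) = 2.705; Φ(2/2.705 − 1.96) = Φ(−1.22) = 11.1%.
- Corrected: n₁ = 139, μ = 2; Φ(0 − 1.96) = 2.5%.
- ITT: SE = 10 × √(2/154) = 1.140, μ = 1.8; Φ(0.2/1.140 − 1.96) = Φ(−1.78) = 3.7%.

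**False non-inferiority with the true effect in users at the margin**

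| Non-uptake p | HealthCap patients in PP as written | PP as written, 0.025 | PP corrected, 0.025 | ITT, 0.025 | PP as written, 0.0125 | PP corrected, 0.0125 | ITT, 0.0125 |
|---|---|---|---|---|---|---|---|
| 5% | 8 | 8.0% | 2.5% | 3.1% | 4.6% | 1.25% | 1.6% |
| 10% | 15 | 11.1% | 2.5% | 3.7% | 6.7% | 1.25% | 1.9% |
| 20% | 31 | 17.3% | 2.5% | 5.4% | 11.0% | 1.25% | 2.9% |
| 30% | 46 | 22.1% | 2.5% | 7.6% | 14.7% | 1.25% | 4.3% |
| 50% | 77 | 29.9% | 2.5% | 14.0% | 20.9% | 1.25% | 8.6% |

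In every row the set as written is less protective than the ITT analysis it is meant to check.

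**Precision of the set as written.** The 95% half-width is 1.96 × SE: 5.3 mmHg with 15 HealthCap patients, 3.9 with 31 and 3.3 with 46, against a margin of 2 mmHg.

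**The case against.** Four points can be made for the plan.

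1. **It is probably a slip.** The sentence before it is garbled, and the purpose stated just above it is the conventional one. A sensible analyst would be unlikely to drop every HealthCap user. This is fair, but the sentence is grammatical, nothing else corrects it, and it is the text that will be followed or cited.

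2. **PP is only a sensitivity analysis.** No sentence makes the non-inferiority conclusion depend on it. This stands: the primary result, the sample size and trial conduct are untouched.

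3. **So small a set would usually fail to show non-inferiority.** With half-widths of 3.3 to 5.3 mmHg around a difference near zero, the upper limit would exceed 2 mmHg about 78% to 89% of the time (p from 30% to 10%). If HealthCap truly makes no difference, the set as written shows non-inferiority less often than a correct one: at p = 10%, 11% against Φ(2/1.170 − 1.96) = 40%. This stands as arithmetic. But protection against a false claim is judged when the true effect is at the margin, and there the set as written is the permissive one. When HealthCap does no harm, the set is merely uninformative.

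4. **Non-users are self-selected.** They may have higher BP than controls. If by about 2 mmHg, the expected difference in the set as written becomes 2 mmHg and the false-claim rate returns to 2.5%. The direction of bias is therefore an expectation under an assumption. Even so, the comparison would reflect who declines HealthCap and say nothing about its effect.

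**Conclusion.** The definition is wrong as written and contradicts the purpose stated for it in the same paragraph. With the true effect at the margin, 10% to 30% non-uptake, SD 10 mmHg and about 154 evaluable per arm, it raises false non-inferiority in the PP analysis from 2.5% to between 11% and 22% at one-sided 0.025. At 0.0125 the rise is from 1.25% to between 6.7% and 14.7%.

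The non-uptake rates are assumed, and the size rests on non-users resembling usual-care patients. The damage is confined to a sensitivity analysis, but that analysis is the safeguard the article names against a false non-inferiority claim, so the definition must be corrected before analysis.

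**What to change.** Replace the sentence with a definition along these lines: the PP population comprises participants in the mITT set who received their allocated strategy without major protocol deviation. Then state:

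- **HealthCap arm:** the participant transmitted home readings and completed the safety questionnaire at the scheduled refill cycles. Those sent to a consultation by the algorithm stay in, in line with the section on modifying allocation.
- **Control arm:** the participant took up no new hypertension app.
- **Reporting:** the PP interval is set against the same 2 mmHg margin as the primary analysis.

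The minimum share of refill cycles and the list of major deviations can sit in the statistical analysis plan, if fixed before the allocation code is broken for analysis. The garbled mITT sentence should be rewritten at the same time, since PP is built on it.

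The cost is a wording amendment. The trial was still recruiting when the article was written (114 of 365 under Trial status), and the article sets out an amendment route. New app use in controls is recorded at 6 and 12 months. Home readings reach the clinic and the questionnaire is online, but the article does not list transmission or questionnaire completion as retained trial data, so the team should confirm that these logs are kept. Settling the definition now also avoids choosing the PP set after the results are known.

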### Outcome measures

#### Primary outcome: daytime ABPM BP at 12 months

ABPM is the reference standard for BP measurements because of its superior reproducibility and predictability of cardiovascular outcomes [13, 14]. Mean daytime SBP will be the primary outcome of the RCT. SBP instead of DBP will be our primary outcome because SBP is more predictive of cardiovascular events than DBP, especially in the elderly [18]. WatchBP O3 (Microlife AG, Switzerland) has been validated by multiple HT societies (www.stridebp.org) and will be used in the current RCT. ABPM will be conducted in accordance with international guidelines (including the use of the non-dominant arm and appropriate cuff size) [19]. BP will be measured every 30 min for ≥24 h, and patients’ sleep diary will define the sleep duration. The readings will be considered valid if there are >70% valid readings overall, >20 valid awake, and >7 valid asleep BP readings in 24-h intervals [19]. Furthermore, erroneous and physiologically impossible BP readings are excluded (i.e. SBP outside the range of 50–240 mmHg and DBP outside the range of 40–140 mmHg) [19].

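### The single primary non-inferiority decision is tied to both a 0.0125-level test and a 95% confidence interval, and these two rules can disagree

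*Protocol article*

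**What the plan says.** In the protocol article, under Statistical analysis, the margin is fixed first: "we set the non-inferiority margin for ABPM SBP at 2 mmHg". The next sentence gives the rule for accepting non-inferiority. It places the decision "in a 0.0125-level test after Bonferroni correction for multiple testing", and makes acceptance depend on an interval bound: "if the lower bound of the two-sided 95% confidence interval (CI) (equivalent to the upper bound of the one-sided 97.5% CI". The text does not say whether 0.0125 is one-sided or two-sided, or which tests the correction covers.

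Under Primary outcome there is a single variable: "Mean daytime SBP will be the primary outcome of the RCT", taken at 12 months. Trial design describes two parallel arms, so there is one contrast. Statistical analysis labels the per-protocol analysis a sensitivity analysis.

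Under Sample size calculation the trial is sized by "setting type I error at 5% and type II error at 20" per cent, with "a standard deviation (SD) of 10 mmHg on ABPM". No sidedness is given there either.

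**The concern.** A test level and a confidence level are two descriptions of the same rule only if they correspond. Here they do not. A bound of a two-sided 95% CI is a one-sided test at 0.025, while the stated test level is 0.0125. Both are attached to one decision, and nothing elsewhere in the article says which governs.

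That decision is the trial's only confirmatory claim. It also determines whether the cost-minimisation analysis in the secondary objectives goes ahead. The article says that investigators cannot be blinded after randomisation (the analysing statisticians stay blinded). If the level is still open when the results are known, it could be chosen in the light of them.

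**Working it through.** **Inputs from the article.** Margin 2 mmHg; SD 10 mmHg; type I error 5% (sidedness not given); power 80%; 309 before dropout and 364 after 15% dropout; 1:1 allocation; ANCOVA on baseline ABPM systolic BP.

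**Assumptions, not in the article.** True difference 0. Share of variance explained by baseline (r-squared) shown at 0 and at 0.50, because no baseline correlation is given.

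**1. Which level lies behind 309?** Per arm, n = 2 × [SD × (z(1-α) + z(0.80)) / margin]².

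- One-sided 0.05: 2 × [10 × (1.6449 + 0.8416) / 2]² = 309.13.
- One-sided 0.025: 2 × [10 × (1.9600 + 0.8416) / 2]², rounded up, = 393.
- One-sided 0.0125: 476. One-sided 0.00625: 558.

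Of these, only one-sided 5% returns 309, and it does so as a per-arm number. The article uses 309 as the total, since 309 / 0.85 = 363.5, or 364. To be a total, 309 would need an unstated r-squared of 1 - 309/618.26 = 0.50 at one-sided 5%, or about 0.61 at one-sided 2.5%. So 309 suggests a one-sided 5% level but does not prove it.

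**2. Which interval goes with which test?**

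| Statement | One-sided level | Matching two-sided CI |
|---|---|---|
| 95% CI bound, as written | 0.025 | 95% |
| 0.0125 test, if one-sided | 0.0125 | 97.5% |
| 0.0125 test, if two-sided | 0.00625 | 98.75% |

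On neither reading does the 0.0125 test match the 95% CI. One-sided p-values from 0.0125 to 0.025 (from 0.00625 if the test is two-sided) pass one rule and fail the other. This step uses no SD, sample size or correlation.

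**3. Where could 0.0125 come from?** It equals 0.05/4 or 0.025/2. The article names no set of four or of two confirmatory tests.

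**4. Size of the disputed zone, 309 completers in total.** The difference is telemedicine minus usual care. SE = 10 × √(2/154.5) = 1.138 mmHg without covariate gain, and 1.138 × √0.50 = 0.805 mmHg with r-squared 0.50. Success requires an observed difference below 2 - z × SE. Power = Φ(2/SE - z).

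| Rule | z | Cut-off, r² = 0 | Power | Cut-off, r² = 0.50 | Power |
|---|---|---|---|---|---|
| 95% CI (0.025) | 1.960 | -0.23 mmHg | 42% | +0.42 mmHg | 70% |
| One-sided 0.0125 | 2.241 | -0.55 mmHg | 31% | +0.20 mmHg | 60% |

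The loss is 42.0 - 31.4 = 10.6 points in the first case and about 10 in the second. It is also the chance, if the true difference is 0, that the result falls where the two rules disagree.

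**5. Example, r-squared 0.** Suppose the observed difference is -0.35 mmHg. The upper 95% limit is -0.35 + 1.960 × 1.138 = 1.88, below 2: success. The upper 97.5% limit is -0.35 + 2.241 × 1.138 = 2.20, above 2, and the one-sided p is 0.019, above 0.0125: failure.

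**The case against.** The best defence is that the article condenses a fuller protocol, and that a statistical analysis plan not shown may name the family of tests. The article does mention per-protocol and subgroup analyses, several other BP outcomes, and possible interim results in a report to the funder. That is fair as far as it goes: one can say that no family is named, not that none exists. But naming a family would not make a 95% CI agree with a 0.0125 test. The article does not leave alpha to another document; it states two values for it.

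Three stronger readings are tempting, and the article does not support them.

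- A reader might infer that three incompatible levels are established, counting the 5% in the sample size. Sidedness is not stated there, and two-sided 5% would agree with the 95% CI. One-sided 5% is inferred from a figure that matches only per arm, and how 309 is used is a separate question.
- A reader might infer that type I error is inflated or has no limit. Every level in the decision sentence is at or below one-sided 0.025. The defect is ambiguity about success. Only the inferred one-sided 5% is looser, and it is not part of the decision rule.
- A reader might take 42% and 31% as the trial's power. They ignore any gain from the planned ANCOVA. At an assumed r-squared of 0.50 they become about 70% and 60%.

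**Conclusion.** The decision rule is wrong as written: one sentence sets two levels for the single primary claim, and no other section settles which applies. This is certain and needs no assumption. The Bonferroni family is unidentified, against a stated design of one primary outcome, one contrast and one primary time point.

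The practical size does rest on assumptions (309 completers in total, SD 10 mmHg, true difference 0). The position of the disputed zone moves with the baseline correlation. The power cost of the stricter rule hardly does: about 10 to 11 percentage points in both cases shown. That the sample size used a third, looser level is a reasonable suspicion, not a finding. The point must be fixed because of the contradiction in the decision sentence, and not because of the power figures.

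**What to change.** Before any outcome data are analysed, state one alpha with its sidedness and give the CI level that corresponds to it.

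- **Simplest form, as no family is named:** delete the 0.0125 and Bonferroni clause. Declare non-inferiority at one-sided 0.025 if the upper limit of the two-sided 95% CI for telemedicine minus usual care is below 2 mmHg. Describe secondary outcomes as supportive. Stating the direction of the difference also settles whether the lower or the upper bound is meant.
- **If a confirmatory family does exist:** name its members, keep 0.0125, and widen the interval to two-sided 97.5% (98.75% if the test is two-sided).

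In either case, state the sidedness of the 5% under Sample size calculation and restate power at the chosen level, with any assumed baseline correlation made explicit.

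The rule itself is a wording change, but it has costs. The first option takes the more lenient of two published rules after recruitment has begun (114 of 365 at the time of the article), so it should be dated, justified and approved through the article's own amendment procedure. The stated power will also look less favourable. At one-sided 0.025 without covariate gain, 80% power needs 786 evaluable participants (925 with 15% dropout), so the sample size has to be rechecked.
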